**Participants 6**

**Intervention 6**

**Outcome measurements 9**

**Adverse events 9**

**Quality control 10**

**References 11**

**Table of Abbreviations**

| **Abbreviations** | **English name** |
| --- | --- |
| ACEI | Angiotensin-Converting Enzyme Inhibitors |
| ADA | American Diabetes Association |
| AE | Adverse event |
| ALT | Alanine aminotransferase |
| ARB | Angiotensin Receptor Blocker |
| AST | Aspartate aminotransferase |
| BUN | Blood urea nitrogen |
| Cr | Creatinine |
| CRF | Case Report Form |
| DKD | Diabetic Jidney Disease |
| DM | Diabetic Mellitus |
| eGFR | estimated Glomerular Filtration Rate |
| FBG | Fasting Blood Glucose |
| HbA1C | Hemoglobin A1C |
| HDL-C | High Density Lipoprotein-Cholesterol |
| ICF | Informed Consent Forms |
| IEC | Independent Ethics Committee |
| LDL-C | Low Density Lipoprotein-Cholesterol |
| SAE | Serious Adverse Event |
| SFDA | China’s State Food and Drug Administration |
| SOP | Standard Operating Procedure |
| TC | Total Cholesterol |
| TCM | Traditional Chinese medicine |
| TG | Triglyceride |

**Background**

Diabetic mellitus (DM) is a lifelong progressive disease, usually associated with various complications in its late stage, which could cause great challenges and burdens to patients, their families, health care system and national economics. The prevalence of DM all over the world was 5.1% in 2003. The prevalence of DM in China also has a tendency to increase and reached to 5.5% in 2001[[[1]](#endnote-2)].

Diabetic kidney disease (DKD) is one of the most common microvascular complications of diabetes mellitus, and it has become the second cause of end-stage renal disease (ESRD) in China [[[2]](#endnote-3)]. Up to now, there is no proved therapy to cure or prevent the progression of DKD, though some reports showed that good management of blood glucose, blood pressure and blood lipid and medicine application of Angiotensin-converting enzyme inhibitors（ACEI）or Angiotensin Receptor blockers (ARB) might postpone the disease’ progression [[[3]](#endnote-4),[[4]](#endnote-5)]. Traditional Chinese medicine (TCM) has been applied to treat DKD for a long history, and recently several studies have reported some advantages of TCM in ameliorating clinical symptoms, improving quality of life, decreasing urinary protein excretion and improving renal function [[[5]](#endnote-6)-,[[6]](#endnote-7),[[7]](#endnote-8)]. Nevertheless, these trials of either small sample size or lack of placebo-controlled arm or low quality monitoring and management of study process take high risk bias to these evidences to support the effects of TCM. Hence, it is necessary and urgent to conduct a well-designed high quality RCT to assess the efficacy and safety of TCM for the treatment of DKD patients.

**Trial objectives**

To evaluate the efficacy and safety of TSF in treating diabetic kidney disease.

**Study design**

The study is designed as a randomized, double-blinded, placebo-controlled trial. It will be conducted in the following six hospitals: China-Japan Friendship Hospital, Bejing; Longhua Hospital affiliated to Shanghai University of TCM, Shanghai; Dongzhimen Hospital affiliated to Beijing University of Chinese Medicine; Hebei United University School of Medicine Affiliated Hospital, Tangshan; Kailuan Hospital, Tangshan; and Tangshan Workers Hospital, Tangshan. Figure 1 is a flow chat of this trial.

**Sample size**

The sample size has been calculated according to our preliminary results [[[8]](#endnote-9)]. The mean reduction of UAER in the control group was 30.19, and that in TSF group was 81.67. The ratio of patients between the treatment group and the placebo group is designed as 2:1. The sample size has been estimated to be 56 in the control group, and 112 in the treatment group. Assuming a dropout rate of 15%, 90% power to detect and a 0.05 two-side level of significance, the sample size of DKD patients has been estimated to be 192.

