**Inclusion and exclusion criteria**

Patients aged 25-75 years who have been diagnosed as type 2 diabetes and DKD will be included in the study and meet the following inclusion criteria: the Chinese syndrome differentiation type as Qi and Yin deficiency with blood stasis; blood pressure < 140/90mmHg; fasting blood glucose (FBG) ≤ 7.8 mmol/L and glycosylated hemoglobin (HbA1C) ≤7.5%; UAER>20 μg/min , and/or 24-hour urinary protein level 0.5~2.0 g, and estimated glomerular filtration rate (eGFR) estimated by Cockcroft-Grault equation ranging from 60ml/min to130ml/min; signed written informed consent.

Patients will be excluded if they had a history of primary kidney diseases or systematic disease with elevated urinary protein. Other major exclusion criteria were other endocrine or metabolic disease; mental disorders; women in pregnancy or lactation; herb allergy; a history of myocardial infarction, angina pectoris or other recent cardiovascular problems (including cerebrovascular events) within the last 3 months or recent infection within the last 4 weeks; fasting serum triglyceride > 10 mmol/L; impaired hepatic function, defined as Alanine transaminase (ALT) and/or Aspartate aminotransferase (AST) level≥2 times the upper limit of the nomal reference range. Patients who take glucocorticosteroid, thiazide diuretics and niacin within the last 3 months will also be excluded.

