**Outcome measurements**

**Primary outcomes**

UAER for DKD patients in the microalbuminuria stage and 24-hour urinary protein excretion amount for DKD patients in the macroalbuminuria stage are considered as the primary outcome measurements.

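### The 90% power is calculated for one UAER comparison on all 168 evaluable patients, so it is not supported for either of the stage-specific primary comparisons

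*Protocol*

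**What the plan says.** The Sample size section of the protocol bases the calculation on one earlier study ("The sample size has been calculated according to our preliminary results") and on one variable: "The mean reduction of UAER in the control group was 30.19, and that in TSF group was 81.67". It gives no unit, no standard deviation and no disease stage for these means. Allocation is two to one, and the result is: "The sample size has been estimated to be 56 in the control group, and 112 in the treatment group". The operating values are given as "Assuming a dropout rate of 15%, 90% power to detect and a 0.05 two-side level of significance", and the total after dropout is 192.

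The Primary outcomes section defines the primary measure by stage: "UAER for DKD patients in the microalbuminuria stage and 24-hour urinary protein excretion amount for DKD patients in the macroalbuminuria stage".

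Both stages are enrolled. The diagnosis criteria name both, the flowchart screens for both, and the inclusion criteria admit patients by either measure: "UAER>20 μg/min , and/or 24-hour urinary protein level 0.5~2.0 g". The protocol gives no target number or share per stage, and the randomization section mentions no stratification by stage. The flowchart lists both urinary measures as primary without tying either one to a stage.

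**The concern.** The sample size calculation and the primary outcome describe different comparisons. The calculation lets every evaluable patient contribute a UAER change to one test. The outcome definition lets only the microalbuminuria patients do so. The remaining patients contribute a different variable, for which the protocol states no expected difference, no spread and no required number.

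This is the only power statement in the protocol, and it is not tied to the stated primary outcome. If the two stages are reported separately, a non-significant result in one of them would be read against a 90% claim that was never worked out for it. A reader could then take an inconclusive result as evidence that the treatment does not work.

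**Working it through.** **Inputs from the protocol (Sample size).** Mean UAER reductions of 81.67 and 30.19, so the difference is 81.67 − 30.19 = 51.48. Evaluable patients 56 and 112, together 168. Two-sided alpha 0.05, power 90%.

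**Step 1: the plan's own figure.** No SD is stated, so 56 + 112 cannot be reproduced independently. It can only be solved backwards for the SD that it implies. With the normal approximation:

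SD = difference / [(z₀.₉₇₅ + z₀.₉₀) × √(1/56 + 1/112)]

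- √(1/56 + 1/112) = √(1.5/56) = 0.1637
- (1.960 + 1.282) × 0.1637 = 0.5305, the implied standardised effect
- SD = 51.48 / 0.5305 = 97.0

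A two-sample t calculation gives nearly the same: standardised effect 0.534, SD 96.5. The stated 168 is thus consistent with one UAER test on all evaluable patients at an SD of about 97.

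**Step 2: what the outcome definition leaves for UAER.** Let f be the share of the 168 in the microalbuminuria stage. The protocol does not give f, so a range is shown. Assume that the standardised effect found in step 1 also holds within that stage, that the 2:1 ratio holds there, and that the test is two-sided at 0.05. Then

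power ≈ Φ(0.5305 × √(56f/1.5) − 1.960) = Φ(3.2415 × √f − 1.960)

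| Share f (assumed) | Patients in stage | Power, normal approximation | Power, t test |
| --- | --- | --- | --- |
| 30% | 50.4 | Φ(−0.185) = 43% | 42% |
| 50% | 84.0 | Φ(0.332) = 63% | 62% |
| 70% | 117.6 | Φ(0.752) = 77% | 77% |
| 90% | 151.2 | Φ(1.115) = 87% | 87% |
| 100% | 168.0 | Φ(1.282) = 90% | 90% |

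The expression rises with f and reaches 90% only at f = 1. Under the stated assumption, any mix of stages puts the UAER comparison below 90%. The table takes the 168 at face value. Fifteen percent loss from 192 leaves 192 × 0.85 = 163.2 evaluable patients, and the first three t-test entries then become 41%, 61% and 76%.

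**Step 3: how far the assumption matters.** For 90% power with 84 patients (28 and 56), the normal approximation needs a standardised effect of 3.2415 × √(1.5/28) = 0.75. With the same mean difference, that is an SD of 51.48 / 0.75 ≈ 68.6 in place of 97.0. The protocol gives nothing that would confirm or exclude such a value within the stage.

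**Step 4: 24-hour protein.** The protocol states no expected difference, no SD and no number of patients for this measure. Its power cannot be calculated. It would mirror the table, with 1 − f in place of f, only if its standardised effect were also about 0.53, and no text says so.

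**The case against.** Four things can be said for the plan.

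- **A single test may be intended.** The flowchart names both measures without the stage restriction, and Table 1 schedules both in every patient, so a UAER test on everyone is feasible. A statistical analysis plan, not available here, might also combine the stages in one test with power near 90%. However, the Primary outcomes section is the more specific text and restricts each measure to a stage. The protocol describes no combined test, and a later plan would not make the Sample size section a correct statement about the primary outcome as now defined.
- **The effect may be larger within a stage.** The mean difference and the SD could both differ by stage, so 0.53 need not carry over. This stands. The figures in the table are illustrations under a named assumption and not estimates of the trial's true power.
- **How the two measures are tested together is commonly left to the analysis plan.** This also stands. No multiplicity rule is stated, so power at a split alpha would rest on a rule that the protocol does not contain.
- **No sum is wrong.** True: the defect is a mismatch between the sized comparison and the defined outcome.

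A reader might go further and infer that the planning means come from a mixed-stage population and are too large for microalbuminuria. The protocol does not support that. It gives neither the unit nor the stage of those means, and no baseline distribution.

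**Conclusion.** The point holds as a mismatch between two sections of the protocol. The 90% belongs to one UAER comparison on all 168 evaluable patients. The primary outcome uses UAER in one stage only and 24-hour protein in the other, so the stated power is unsupported for both stage-specific comparisons, and nothing else in the protocol closes the gap.

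For UAER, if the implied standardised effect of about 0.53 holds within the microalbuminuria stage, power is about 42% to 77% for assumed shares of 30% to 70%, and under 90% for any share below 100%. For 24-hour protein, power is unknown.

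It is tempting to conclude that neither comparison has 90% power, or that the trial is underpowered. That is not shown. The first needs the constant-effect assumption for UAER and planning figures for 24-hour protein that do not exist. The second also depends on how the two measures are finally tested. The statement needs correcting because it concerns the trial's only power claim and its primary outcome.

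**What to change.** Either of two changes would do, and neither adds patients.

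1. **Restate the power (Sample size section).** Say that 90% applies only if all 168 evaluable patients enter one test. Give the power of each stage-specific comparison over a stated range of stage shares, with the unit, SD and effect assumed for each measure. If no planning figures exist for 24-hour protein, say so.
2. **Define one primary test (Primary outcomes section).** Use every patient's stage-specific measure in a single comparison of the arms, stratified by stage and adjusted for baseline. State the power of that test under its own named assumptions, and report the stage-specific results as supporting. The two measures need a common scale. The existing planning figures are absolute UAER reductions, so any common effect on the new scale would be a fresh assumption and should be labelled as one.

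With either option, bring the flowchart's primary outcome into line with the text.

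The cost is protocol wording and a less favourable stated power for the stage-specific comparisons. If the trial team wants 90% power for each stage separately, restating is not enough. It would need stage-specific planning values that support that power, or more patients.

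### With the stated 15% dropout, 192 randomised patients leave about 163 evaluable, 5 short of the protocol's own 168; the effect on power is minor

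*Protocol*

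**What the plan says.** All the figures stand in the Sample size section of the protocol. The effect comes from a preliminary study: "The mean reduction of UAER in the control group was 30.19, and that in TSF group was 81.67". No standard deviation is given. On allocation: "The ratio of patients between the treatment group and the placebo group is designed as 2:1". The requirement is then stated: "The sample size has been estimated to be 56 in the control group, and 112 in the treatment group". The last sentence gives the remaining assumptions, "Assuming a dropout rate of 15%, 90% power to detect" and "a 0.05 two-side level of significance", and ends with "the sample size of DKD patients has been estimated to be 192".

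The Randomization and concealment section uses 192 again as the size of the random allocation sequence. It is therefore the working number of the trial and not a slip in one sentence. Nowhere does the protocol say how the dropout allowance was applied.

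**The concern.** The natural reading is that 168 is the number needed for analysis and 192 the number to randomise so that 168 remain after dropout. If 15% drop out, 85% remain, and 85% of 192 is less than 168. The requirement of 168, the dropout of 15% and the total of 192 therefore cannot all hold, and 90% power is tied to the 168.

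What is at stake is the accuracy of a basic design statement. At the dropout it plans for, the trial would miss its own evaluable target. That is visible from three printed numbers and needs no outside information.

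**Working it through.** **Inputs** (all from the protocol, Sample size section): 56 control and 112 treatment patients; dropout 15%; power 90%; two-sided significance level 0.05; ratio 2:1; total 192; difference in mean UAER reduction 81.67 - 30.19 = 51.48, with no standard deviation.

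**Step 1: can 192 be reproduced?**
- Multiplying by 1 + dropout: 168 x 1.15 = 193.2 in total; by arm, 56 x 1.15 = 64.4 and 112 x 1.15 = 128.8.
- Rounding each arm down gives 64 + 128 = 192, which keeps 2:1. Rounding 193.2 down to a multiple of 3 also gives 192.
- This is an inference about the route. The protocol does not describe it.

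**Step 2: the number that offsets 15% dropout.** If a fraction d is lost, the number to randomise is N / (1 - d).
- Total: 168 / 0.85 = 197.6.
- By arm: 56 / 0.85 = 65.9, so 66; 112 / 0.85 = 131.8, so 132.
- Sum: 66 + 132 = 198, which is 6 more than 192 (6 / 192 = 3.1%).

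**Step 3: what 192 delivers.**
- Expected completers: 192 x 0.85 = 163.2, made up of 64 x 0.85 = 54.4 on placebo and 128 x 0.85 = 108.8 on TSF.
- Shortfall: 168 - 163.2 = 4.8, about 5 patients.
- Dropout at which 192 leaves exactly 168: 1 - 168/192 = 12.5%.

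**Step 4: the effect on power.** Without a standard deviation, the step from the UAER difference to 56 and 112 cannot be checked. Assume instead that 56 and 112 are the rounded-up sizes for 90% power in a two-sample t-test at two-sided 0.05. The unrounded control requirement then lies between just above 55 and 56. For each end, solve for the standardised difference that gives 90% power, then compute power at 54.4 and 108.8:

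| Control requirement before rounding | Implied standardised difference | Power at 54.4 / 108.8 |
| --- | --- | --- |
| 56 | 0.534 | 89.1% |
| just above 55 | 0.539 | 89.7% |

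A normal approximation confirms this. The required sum of normal quantiles is 1.960 + 1.282 = 3.242. With 56 as the requirement, 3.242 x sqrt(54.4/56) - 1.960 = 1.235, which is a power of 89.2%. With 55, 3.242 x sqrt(54.4/55) - 1.960 = 1.264, which is 89.7%.

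The loss against 90% is thus about 0.3 to 0.9 percentage points.

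**The case against.** The strongest reply is that this is too small to matter. The dropout allowance was made, perhaps by a familiar shortcut; the gap is 6 randomised patients or 5 completers, and at the favourable end of the range power still rounds to 90%. On size, that stands. On the figures, it does not: multiplying by 1.15 does not offset a 15% loss, since even 193.2 x 0.85 = 164.2 is below 168, and nothing else in the protocol reconciles the numbers.

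A second reply is that power cannot be checked without a standard deviation. This holds in part. The shortfall in patients needs no standard deviation, but any power figure is back-solved and must be labelled an assumption. It also treats all completers as one UAER comparison, while the Primary outcomes section assigns UAER to microalbuminuria patients and 24-hour urinary protein to macroalbuminuria patients. The 89% therefore describes the loss within the protocol's own calculation and is not an independent estimate of the trial's power.

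Three stronger readings are tempting, and the documents support none of them:
- **That the shortfall leaves the trial materially underpowered.** Under the stated assumption the loss is below one percentage point.
- **That the intended dropout was 12.5%.** That value only makes 192 fit; the protocol gives no basis for it as an expectation.
- **That 198 patients must be enrolled.** This follows only if both 15% dropout and the full 168 are to be kept.

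**Conclusion.** The point holds as a minor arithmetic inconsistency. At the stated 15% dropout, 192 randomised patients leave about 163 evaluable, against a requirement of 168; 198 (132:66) would be needed to keep 168. This part rests on printed figures alone, read in the natural way: 168 before dropout and 192 after the allowance for it.

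The consequence for power is slight: about 89.1% to 89.7% in place of 90%, on the assumption that 56 and 112 are the rounded-up t-test sizes for 90% power at two-sided 0.05. The origin of 192 in a 1.15 multiplier rounded down in each arm is plausible but not documented. Neither the design nor the validity of the trial is in question here. What needs correcting is the sample-size statement.

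**What to change.** Keep 192 and the 15% dropout assumption, and restate the end of the Sample size section in one of two ways:

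- Say that 192 randomised patients (64 placebo, 128 TSF) with 15% dropout give about 163 expected completers (about 54 placebo and 109 TSF), and that power is then slightly below 90%, about 89%, on the assumption that 56 and 112 are the t-test sizes for 90% power.
- Or say that 192 preserves 168 evaluable patients only if dropout does not exceed 12.5%. This should read as a condition, not as a new dropout expectation.

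Either costs one sentence and leaves the randomisation list untouched; the claim becomes slightly less favourable. If the sponsor prefers to keep both 15% dropout and 168 evaluable patients, the consistent total is 198 (132:66). That means enrolling 6 more patients and also changing the 192 in the Randomization and concealment section.

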**Randomization and concealment**

The randomization of the trial will be completed by an independent clinical research coordinator, project department of World Federation of Chinese Medicine Societies. 192 seeds and 6 blocks were set to generate the random allocation sequence according to the method of blocked randomization. Investigators of each center sequentially enroll patients according to their consultant order. The randomization sequence will be kept by project department of World Federation of Chinese Medicine Societies, and it will be disclosed after the trial finally finished except for emergency during this trial (such as severe adverse event). Drug administrator in every center is an independent researcher, who is in charge of supervision, dissemination and compliance recording of the drugs. They have the random sequence of their own center in order to dispense drugs

**Blindness**

Double-blinding method is adopted in this study. As the package, color, smell and taste of the placebo is the same as TSF, so researchers and participants won’t know the kind of medicine and group allocation. It was not allowed for the drug administrator to neither contact with investigators, nor exchange information with patients. They are trained how to illustrate the usage and dose of this formula for the patients but not to convey any treatment information to participants.

The outcome assessment will be conducted by independent researchers who don’t know the group allocation of patients.

Figure 1: The flowchart of the trial:

Screening for type 2 diabetic kidney disease with microalbuminuia /marcoalbuminuia individuals

Sign consent

Inclusion criteria achieved?

Run-in period (2 weeks)

NO

Excluded

Primary outcome:

UAER & 24h urinary protein

Secondary outcome (1):

Scr，BUN， eGFR

Blood lipid

Secondary outcome (2):

TCM syndrome & quality of life

Completed the 24-wk administration

**TSF group**：

TSF+ACEI/ARB

**Placebo group**： Placebo + ACEI/ARB

Visits and clinical measurements, medication

at 4,8,12,16,20,24 weeks

YES

Randomization

**Patient ratio**

**2 : 1**

**Participants**

**Diagnosis criteria**

Patients with type 2 diabetes are diagnosed according to the American Diabetes Association criteria [[[9]](#endnote-10)],and micro-albuminuria and macro-albuminuria stages of DKD are defined in the light of the K-DOQI guidelines [[[10]](#endnote-11)], and the Chinese syndrome differentiation type as Qi and Yin deficiency with blood stasis is based on the guiding principle of clinical research on new drugs of traditional Chinese medicine [[[11]](#endnote-12)].

**Inclusion and exclusion criteria**

Patients aged 25-75 years who have been diagnosed as type 2 diabetes and DKD will be included in the study and meet the following inclusion criteria: the Chinese syndrome differentiation type as Qi and Yin deficiency with blood stasis; blood pressure < 140/90mmHg; fasting blood glucose (FBG) ≤ 7.8 mmol/L and glycosylated hemoglobin (HbA1C) ≤7.5%; UAER>20 μg/min , and/or 24-hour urinary protein level 0.5~2.0 g, and estimated glomerular filtration rate (eGFR) estimated by Cockcroft-Grault equation ranging from 60ml/min to130ml/min; signed written informed consent.

Patients will be excluded if they had a history of primary kidney diseases or systematic disease with elevated urinary protein. Other major exclusion criteria were other endocrine or metabolic disease; mental disorders; women in pregnancy or lactation; herb allergy; a history of myocardial infarction, angina pectoris or other recent cardiovascular problems (including cerebrovascular events) within the last 3 months or recent infection within the last 4 weeks; fasting serum triglyceride > 10 mmol/L; impaired hepatic function, defined as Alanine transaminase (ALT) and/or Aspartate aminotransferase (AST) level≥2 times the upper limit of the nomal reference range. Patients who take glucocorticosteroid, thiazide diuretics and niacin within the last 3 months will also be excluded.

